### 2.2. Study Objectives

#### 2.2.1. Primary Objectives

To determine the relationship between the predominant composition of the human gastrointestinal microbiome and the objective response to treatment with ICIs in patients with metastatic malignant melanoma.To determine whether the dynamics of exosomal mRNA expression for PD-L1 and PD-L1 on the surface of immune cells is related to the response to immunotherapy treatment and has predictive value.To determine whether the exosomal mRNA expression for IFNγ is related to the response to immunotherapy treatment and has a predictive value.

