#### 2.5.4. Statistical Methods

The gastrointestinal microbiome, PD-L1 and Interferon Gamma expression will be correlated with one year of PFS as the primary outcome of the study. An interim analysis will be made after the first 20 included patients.

We will analyze the 16S rRNA sequences with the appropriate software tools from the Mothur software package, and we will perform analysis of molecular variance (AMOVA) and principal coordinate analysis (PCoA). For the statistical analysis of the differences in the representation of the sequences of individual bacterial groups in the studied microbiomes, we will use the DeSeq 2 package from the R programming environment. The association between phylogenetic diversity, taxonomic units, immune cells and the objective response to treatment will be determined using the Wilcoxon test. To compare values at different time points, we will use the paired *t*-test or corresponding non-parametric alternative. When comparing several groups at the same time, we will use the Kruskal–Wallis test. All differences will be considered statistically significant when *p* < 0.05.

The Kaplan–Meier method will be used to calculate survival (PFS), and the survival comparison of multiple groups will be calculated using the log-rank test. The association between the change in PD-L1 or IFNγ expression and response to treatment will be assessed using a logistic regression model and a multivariate model in which different variables will be included. Pearson’s or Spearman’s correlation test will be used to correlate changes in PD-L1 or IFNγ expression levels in tumor and blood.

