## 3. Discussion

Immunotherapy with immune checkpoint inhibitors has improved the prognosis and survival of patients with metastatic malignant melanoma. Its effect is unpredictable and can cause immune-related adverse events in more than a third of the patients. To avoid high grade immune-related adverse events, rapid disease progression or even hyperprogression, new biomarkers are needed to predict response to ICIs.

The human microbiome is the genetic set of all microorganisms in the digestive tract and, by being involved in innate and acquired immunity, influences the effectiveness of immunotherapy treatment. One of the main objectives is to investigate the possibility of using the GIT microbiome as a tumor biomarker. By analyzing the GIT microbiome, it would be possible to identify patients who will benefit from ICI treatment or who will have a higher risk of side effects, even before the start of treatment. In patients with an unfavorable composition of the microbiome, targeted drugs could be used in the first line of treatment in certain cases, thus avoiding the rapid progression of the disease or the side effects of treatment with ICIs. The results of our research will help to more precisely define which phylotypes in the GIT microbiome are more favorable for ICI treatment. Based on this, in the future, the GIT microbiome could also be modified by influencing lifestyle and diet, by adding oral preparations or by fecal transplantation of the microbiome.

PD-L1 expression is variable and changes dynamically during disease evolution; a one-time biopsy sample from tumor tissue is not representative enough. Minimally invasive and real-time detection within peripheral blood exosomes is far more accurate and could provide a better prognostic marker. Interferon Gamma (IFNγ) also correlates with response to ICIs but its detection remains hard to obtain. With liquid biopsy and real-time exosome expression, we could define the patients with higher level of circulating IFNγ and thus build a better response to immunotherapy. Some recent studies have also shown that gastrointestinal microbiome modulates the IFNγ response.

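### The stated significance rule, p < 0.05 for all differences, gives no multiplicity control for the per-taxon and immune-cell tests that are meant to identify favourable phylotypes

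*Protocol article*

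**What the plan says.** All the relevant text is in the protocol article.

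- **Tests planned (2.5.4 Statistical Methods).** The second paragraph plans AMOVA and principal coordinate analysis of the 16S sequences, and DESeq2 for differences in individual bacterial groups. It then says: "The association between phylogenetic diversity, taxonomic units, immune cells and the objective response to treatment will be determined using the Wilcoxon test". Paired tests between time points and Kruskal-Wallis tests for several groups follow.
- **Decision rule (same paragraph, last sentence).** "All differences will be considered statistically significant when" p < 0.05. No adjustment is mentioned there or elsewhere in the article.
- **Next paragraph of 2.5.4.** Kaplan-Meier and log-rank for PFS, logistic and multivariate models for change in PD-L1 or IFNγ, and tumour-blood correlations. No threshold is given in that paragraph.
- **Primary objectives (2.2.1).** There are three: gut microbiome composition, PD-L1 and IFNγ, each against response. The first reads: "To determine the relationship between the predominant composition of the human gastrointestinal microbiome and the objective response to treatment with ICIs". No single taxon or index is named for it.
- **Time points (2.3.6).** Three scheduled collections plus event samples.
- **Readouts (2.5.1, 2.5.2).** 16S taxonomic units, metagenomic taxonomic and functional profiles, a virome subset, and several T-cell and macrophage subsets with PD-1 and PD-L1 on each.
- **Intended use (3. Discussion).** "The results of our research will help to more precisely define which phylotypes in the GIT microbiome are more favorable for ICI treatment".

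**The concern.** A 0.05 threshold applied test by test holds the error rate of each test. It does not control how many entries on a list of significant taxa are false. The design produces many such tests: each taxonomic unit and each cell subset against response, a second taxon-level analysis by DESeq2, and repeats over time points.

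The Discussion intends to say which phylotypes favour treatment. If the list is drawn up by the written rule, some taxa will appear on it whether or not any is related to response, and a reader cannot tell these from real ones. The larger cohort does not help, because the false-positive rate per test does not depend on sample size.

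This is more than detail left to an analysis plan that is not shown. The article fixes a threshold and gives it the scope of all differences, directly after the taxon-level tests.

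**Working it through.** **The plan's own figure.** The only error-rate figure in the article is the threshold of 0.05. It derives no overall error rate, and the sample size of 150 comes with no power inputs, so there is nothing further to reproduce.

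**Inputs.**
- α = 0.05 per test (2.5.4).
- Three scheduled time points (2.3.6) and three primary biomarkers (2.2.1).
- m, the number of taxa tested: not given. A range of 20 to 200 is assumed.
- Every null hypothesis is taken as true, to show what the rule yields when there is no association.

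**Step 1: expected number of false calls.** E = 0.05 × m. This holds whatever the correlation between taxa.

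**Step 2: chance of at least one false call, independent tests.** P = 1 − 0.95^m.

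| m | Expected false calls | P(at least one) |
|---|---|---|
| 20 | 1 | 64.2% |
| 50 | 2.5 | 92.3% |
| 100 | 5 | 99.4% |
| 200 | 10 | 99.997% |

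P passes 95% at m = 59 (ln 0.05 / ln 0.95 = 58.4) and 99% at m = 90 (ln 0.01 / ln 0.95 = 89.8). With 100 taxa at three time points there are 300 tests and 300 × 0.05 = 15 expected false calls.

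**Step 3: correlated taxa.** Taxa from one stool sample are unlikely to be independent. Test statistics were simulated as equally correlated normals (20,000 replicates, two-sided p-values, m = 100). The last column applies Benjamini-Hochberg at 5% to the same data.

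| Correlation | Mean false calls at p < 0.05 | P(at least one) at p < 0.05 | P(at least one), Benjamini-Hochberg |
|---|---|---|---|
| 0 | 4.97 | 99.5% | 5.0% |
| 0.1 | 5.00 | 99.0% | 5.0% |
| 0.3 | 4.98 | 94.6% | 4.6% |
| 0.5 | 5.02 | 77.8% | 3.4% |
| 0.8 | 4.91 | 35.8% | 1.8% |

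Correlation lowers the chance of any false call but leaves the mean at about 5. The false calls then come in clusters: none in many studies, many in a few. The simulation covers equal positive correlation only.

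**Step 4: the three primary biomarkers alone.** One independent test each gives 1 − 0.95^3 = 14.3%.

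**The case against.** **No text says unadjusted.** A 0.05 cut-off can be applied to adjusted p-values, DESeq2 may be run that way, and a condensed article may leave multiplicity to an analysis plan. It stands that the article does not rule out adjustment, so the accurate description is that none is stated. But adjusted DESeq2 output would not cover the separate Wilcoxon tests of taxonomic units and immune cells, and the published sentence as it reads asks only for p < 0.05.

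**False predictive taxa are not practically certain.** A reader might infer near-certainty across biomarkers, taxa and time points together. The documents do not support that. A figure above 99% needs about 90 or more near-independent taxon tests, and the article gives no count. Three primary tests alone give 14%, and 100 taxa correlated at 0.8 give 36%. Only the expected count is unaffected by correlation.

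**The rule may not reach all primary objectives.** A reader might take the sentence to govern all three alike. It speaks of differences and comes before the paragraph with the regression models for PD-L1 and IFNγ and the log-rank test. Its reach there is plausible but not stated.

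**Each primary objective is its own question.** Whether to adjust across three separate biomarker objectives is debatable, and an overall microbiome test (AMOVA) is already planned. Both points stand, so adjustment across objectives is not treated here as required.

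**The earlier conflicting results.** The rationale (1.2.6) blames animal models and small numbers, not multiple testing. It should not be cited as if it admitted this problem.

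**No patient's treatment depends on a taxon p-value.** The study is non-interventional, and any use is placed in the future. This limits the immediate harm but does not make the list of phylotypes sound.

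**Conclusion.** The concern holds for the taxon-level and cell-subset tests. The article fixes p < 0.05 for all differences straight after them and states no adjustment. With no true association, about 5% of tested taxa would be declared: 5 per 100 at one time point, 15 over three. The chance of at least one false declaration for 100 taxa runs from about 99% if they are independent to about 36% at a correlation of 0.8.

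The expected count assumes only true nulls and valid p-values. The percentages also rest on the assumed number of taxa and on the correlation between them. The documents do not show that false findings are practically certain, or that the same failure extends to the three primary biomarker objectives as a set.

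**What to change.** Replace the closing sentence of that paragraph of 2.5.4 with these rules:

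1. **First primary objective.** AMOVA, already planned, is the single overall microbiome test at 0.05. Name its grouping variable and time point, since 2.2.1 speaks of objective response while 2.5.4 names one-year PFS as the primary outcome.
2. **Taxon, function and cell-subset tests.** Wilcoxon and DESeq2 results alike are declared by Benjamini-Hochberg at a 5% false discovery rate within each family and time point, with the families listed.
3. **Everything else.** P-values outside the named primary tests are labelled exploratory.

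Holm adjustment across the three primary biomarker objectives is optional.

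The cost is one paragraph, with no new samples, assays or patients. Individual taxa lose power: with 100 taxa in a family, a lone finding would need p ≤ 0.05 / 100 = 0.0005. The loss cannot be put as a power figure, because the article gives no effect sizes.

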## Abstract

Background: Immunotherapy has been successful in treating advanced melanoma, but a large proportion of patients do not respond to the treatment with immune checkpoint inhibitors (ICIs). Preclinical and small cohort studies suggest gastrointestinal microbiome composition and exosomal mRNA expression of PD-L1 and IFNγ from the primary tumor, stool and body fluids as potential biomarkers for response. Methods: Patients treated with immune checkpoint inhibitors as a first line treatment for metastatic melanoma are recruted to this prospective study. Stool samples are submitted before the start of treatment, at the 12th (+/−2) week and 28th (+/−2) week, and at the occurrence of event (suspected disease progression/hyperprogression, immune-related adverse event (irAE), deterioration). Peripheral venous blood samples are taken additionally at the same time points for cytologic and molecular tests. Histological material from the tumor tissue is obtained before the start of immunotherapy treatment. Primary objectives are to determine whether the human gastrointestinal microbiome (bacterial and viral) and the exosomal mRNA expression of PD-L1 and IFNγ and its dynamics predicts the response to treatment with PD-1 and CTLA-4 inhibitors and its association with the occurrence of irAE. The response is evaluated radiologically with imaging methods in accordance with the irRECIST criteria. Conclusions: This is the first study to combine and investigate multiple potential predictive and prognostic biomarkers and their dynamics in first line ICI in metastatic melanoma patients.

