#### 1.2.6. Rationale for the Study

The specific composition and biodiversity of the gastrointestinal microbiome, exosomal mRNA expression of PD-L1 and IFNγ and dynamics predict the response to immunotherapy treatment with immune check point inhibitors and could serve as prognostic and predictive markers.

The studies published so far have been carried out on animal models or a small number of subjects or samples. We attribute the conflicting results of the studies conducted so far to this. The importance of intestinal flora in health or pathology and the influence and connection of inflammation and immune cells is a developing medical topic. It is for this reason that many studies are based on small cohorts and a small number of samples, especially in the field of oncology. Our study is pioneering precisely in this respect, as it is composed thoroughly, with a clear hypothesis, on a large cohort and number of samples. Samples will be taken at three different treatment points and at any event such as hyperprogression, pseudoprogression or immune-related side events. We will study the dynamics of changes in the diversity of the GIT microbiome and the systemic immunological response during the treatment of metastatic melanoma with immunotherapy.

The study is first prospective study that simultaneously determines the expression of IFNγ and PD-L1 in tumor tissue and blood at different time points. If we demonstrate that there is a correlation in the expression of IFNγ and PD-L1 in the tumor tissue and the blood, IFNγ could be obtained from the patient’s peripheral blood by a minimally invasive method.

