### 2.4. Biological Sample Collection

#### 2.4.1. Collection of Peripheral Venous Blood Samples

Peripheral venous blood samples will be taken during a regular visit to OI Ljubljana up to 4 weeks before the start of treatment, the 12th (+/−2) and the 28th (+/−2) week, in the event of suspected disease progression/hyperprogression and in the event of the occurrence of immunologically unwanted side effects (colitis or other immune-related side effects).

During regular blood sampling, a sample of blood will be taken from the examinee for additional tests—a total of 10 mL, of which 5 mL will be used for cytologic tests (specific immune host cell concentration) and another 5 mL of the venous blood will be used for molecular tests (messenger RNA for PD-L1 and IFNγ expression).

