#### 2.4.2. Collection of Tumour Samples

Histological material from the tumor tissue will be obtained before the start of immunotherapy treatment. At the Department of Pathology of the Ljubljana Oncology Institute, multitumor blocks and cut material for molecular examinations will be prepared from histological samples.

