#### 2.5.2. Tumor Tissue and Peripheral Blood Analysis

The MagMAX™ FFPE DNA/RNA Ultra Kit will be used to isolate RNA from paraffin. Tissue slices (40 µm) will be prepared from the tumor blocks in the Department of Pathology, after which further analysis will take place in the Department of Experimental Oncology. Initially, the paraffin will be dissolved with the addition of xylene, by centrifugation and heating the samples to 50 °C. This will be followed by rinsing with 100% ethanol and drying the sample with a fixed tissue. The tissue sample will be incubated with protease buffer for 1 h at 50 °C and 1 h at 90 °C. RNA buffer will be added to bind the RNA to the magnetic beads. To remove DNA, a DNAse solution will be added after washing. This will be followed by repeated washing and centrifugation with the elution solution until the RNA supernatant is obtained. The sample will be stored at −80 °C until analysis. Sample analysis will be performed by RT-qPCR.The Plasma/Serum Circulating and Exosomal RNA Purification Kit (Slurry Format (Norgen Biotek Corp., Ontario, Canada)) will be used to isolate RNA from plasma. The analysis will take place on 5 mL of venous blood samples. Blood plasma will be prepared from them by centrifugation. To bind the RNA to the pellets, a 2 mL plasma sample will be incubated with lysis buffer at 60 °C. Then, after adding 100% ethanol, it will be centrifuged. For greater purity, the process will be repeated twice. The ultracentrifugation process will bind the mixture to the column. This will be followed by washing the sample and adding DNase to remove the DNA. The sample will be processed twice more by washing and ultracentrifugation to obtain the supernatant with RNA, which will be stored at −80 °C. RNA concentration will be determined spectrophotometrically with a Qubit fluorometer (Applied Biosystems, Massachusetts, USA). Analysis of the samples is expected to be done by ddPCR.PD-L1 expression on CD4+, CD8+ T lymphocytes and macrophages will be determined using the flow cytometric method. Antibody panels for 7-color flow cytometric measurements (antibodies from BD Biosciences (San Jose, CA, USA), BioLegend (San Diego, CA, USA) and Beckma Coulter (Brea, CA, USA)) will be used. Samples will be measured using a FACSCanto 10 flow cytometer (BD Biosciences). FACSDiva software (BD Biosciences) will be used to analyze flow cytometry results.Serum interferon gamma concentration: Quantikine human IFNγ ELISA kit (R&D Systems™, Minneapolis, USA) will be used to determine serum interferon gamma concentration.For the qRT-PCR assay, SYBR Green chemistry will be used, which enables relative, as well as absolute, quantification of the target sequence in the investigated sample. Relative quantification will be used to determine the expression level of the transgene in the paraffin samples. Additionally, absolute quantification will be used to determine the target sequences in the plasma of the patients using ddPCR. For both relative and absolute quantification, we will use specific set of primers (PrimeTime qPCR Primers, IDT Technologies, Coralville, IA, USA) that do not amplify any other known dsDNA sequence, and are specific for the IFNγ sequence and CD274 (PD-L1) sequence (primer details are in Table 2).Sample preparation for flow-cytometric measurement will be carried out as previously described by our group [38,39]. Used antibodies (Table 3) will be divided into 2 separate tubes according to the analyzed immune cells, and half a million cells per 100 μL will be used for each tube. Immune cells will be gated according to their immunophenotype: T cells (CD3+); the helper T cell subset (CD4+); cytotoxic T cell subset (CD8+); and macrophages (CD11b+CD14+), as well as their M1-like (CD86+) and M2-like (CD206+) subsets. Percentages of T cells and macrophages will be calculated as a ratio per CD45+. Percentages of CD4+ and CD8+ T cell subsets will be given as a percentage of CD3+, while M1-like and M2-like macrophage subsets will be given as a percentage per all macrophages. The expression of PD-1 and PD-L1 will be analyzed on both T cells and macrophages, as well as on their corresponding subsets. The correlation of the analyzed immune cells and their subsets with patient PFS and OS will be also calculated. Survival analysis will be based on an X-year patient follow-up. Flow-cytometric data will be acquired with a 10-color BD FACSCanto™ II Flow Cytometer and FACSDiva 8.0.2 software (BD Bioscience, USA). FSC files will be analyzed using FlowJo v10.8 1 (BD Biosciences, USA).

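### Section 2.5.4 correlates changes in PD-L1 and IFNγ in tumour and blood, but tumour is sampled only once, so the analysis cannot be run as worded

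*Protocol article*

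**What the plan says.** The last sentence of section 2.5.4 (Statistical Methods) plans that Pearson's or Spearman's "correlation test will be used to correlate changes in PD-L1 or IFNγ expression levels in tumor and blood".

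On tumour sampling, section 2.4.2 says: "Histological material from the tumor tissue will be obtained before the start of immunotherapy treatment". The abstract agrees: "Histological material from the tumor tissue is obtained before the start of immunotherapy treatment". Neither mentions a later tissue sample.

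On blood sampling, section 2.4.1 lists "up to 4 weeks before the start of treatment, the 12th (+/−2) and the 28th (+/−2) week, in the event of suspected disease progression/hyperprogression", and also at immune-related side effects.

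Section 1.2.6 describes a study that "simultaneously determines the expression of IFNγ and PD-L1 in tumor tissue and blood at different time points". It gives the purpose of the comparison in a conditional sentence, which opens: "If we demonstrate that there is a correlation in the expression of IFNγ and PD-L1 in the tumor tissue and the blood". The payoff it names is that a simple blood draw might then supply the IFNγ measurement.

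On assays, section 2.5.2 says of tissue: "Relative quantification will be used to determine the expression level of the transgene in the paraffin samples". Of blood it says that "absolute quantification will be used to determine the target sequences in the plasma of the patients using ddPCR".

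**The concern.** A correlation of changes pairs a within-patient difference in one compartment with a within-patient difference in the other. Both compartments need at least two time points, and only blood has them.

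An analyst holding this plan would have to substitute something. Two substitutes are available, and they answer different questions:

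- Baseline tumour level against baseline blood level asks whether patients with high expression in tissue also have high expression in plasma.
- Baseline tumour level against later change in blood asks whether the tissue level before treatment is related to what blood does on treatment.

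Only the first bears on the idea in section 1.2.6 that blood might stand in for tissue. If the choice is left until the data are seen, either result could be reported as the planned tumour-blood correlation.

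**Working it through.** The article gives no figure for this analysis, so there is none to reproduce. The check is a count of time points, followed by a look at what the workable analysis could detect.

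**Step 1: time points per compartment.** With k scheduled samples, a patient has k − 1 changes from baseline.

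| Compartment | Source | Scheduled samples k | Changes k − 1 |
|---|---|---|---|
| Tumour | Abstract; section 2.4.2 | 1 (pre-treatment) | 1 − 1 = 0 |
| Blood | Section 2.4.1 | 3 (baseline, week 12, week 28), plus events | 3 − 1 = 2, plus events |

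The change-to-change correlation needs at least one change in each row. The tumour row has none, so 0 of the 150 planned patients (section 2.1) can contribute.

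**Step 2: what section 1.2.6 asks for.** Its conditional sentence concerns correlation of expression in the two compartments, which is a correlation of levels. One tumour sample and one baseline blood sample per patient are enough for that.

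**Step 3: what the level correlation could detect.** By the Fisher z approximation, with two-sided α = 0.05 and 80% power,

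|r| = tanh[(1.960 + 0.842) / √(n − 3)].

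Section 2.5.4 gives the 0.05 level but not its sidedness; two-sided is assumed, as is the 80% power. The number of usable tissue-plasma pairs is not stated, so a range is shown:

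| n pairs (assumed) | Smallest detectable correlation |
|---|---|
| 150 | 0.23 |
| 120 | 0.25 |
| 100 | 0.28 |
| 75 | 0.32 |

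The formula is for Pearson's coefficient and is only approximate for ranks. The value 150 is a ceiling. Section 2.3.2 admits cytologically verified cases, who may have no histological material, and some tissue or plasma samples may not be usable.

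**Step 4: choice of coefficient.** Tissue is quantified relatively and plasma absolutely. Pearson's r is unchanged if either variable is multiplied by a positive constant or shifted, so different units are no obstacle in themselves. It does change under a non-linear transformation such as a log, and the article states no transformation for either assay. Spearman's coefficient is the same under any increasing transformation, so it leaves nothing to settle on this point.

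**The case against.** The strongest reply is that this is loose wording. Section 1.2.6 shows that a level correlation was meant, and the discussion itself treats a single biopsy as a known limit of tissue. On this view, changes in section 2.5.4 simply means variation in expression. The intent can indeed be recovered, and that limits the harm. But the sentence in the statistical methods is the one an analyst would follow, and it names a quantity the samples cannot give.

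Several stronger readings are tempting, and the document does not support them:

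- *No tumour-blood comparison is possible, so the case for a blood test collapses.* Only the change-to-change version is impossible. The level correlation can be run. It would show association between compartments; like any correlation, it would not show agreement.
- *Pearson is meaningless because the assays use different units.* Step 4 shows otherwise. Spearman is a preference with a reason, and section 2.5.4 already allows it.
- *Table 1 confirms that there is no later biopsy.* Table 1 has no tumour-tissue row at all, even at baseline, so its silence shows nothing. The abstract and section 2.4.2 carry the point.
- *Section 1.2.6 claims repeated tumour sampling.* Its time-point phrase can be read as belonging to blood alone. It is ambiguous and worth clarifying, but it is not a clear second error.
- *The primary results are at risk.* The tumour-blood correlation is not among the primary, secondary or exploratory objectives in sections 2.2.1 to 2.2.3. The logistic models of change against response in section 2.5.4 can use blood changes.

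**Conclusion.** The point holds for the analysis as worded: the tumour change is undefined in every patient, because the article gives one pre-treatment tissue sample and no other. This rests on the abstract and section 2.4.2 being a complete account of tissue sampling. If repeat tissue is planned elsewhere, the error lies in section 2.4.2 instead, and the two sections still need to be reconciled.

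The consequence is contained. One planned analysis outside the listed objectives has to be redefined. The replacement is feasible, with a smallest detectable correlation of about 0.23 to 0.32 for 150 down to 75 pairs under the assumptions above. It should be corrected because the statistical methods and the sampling scheme contradict each other and the repair is almost free.

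**What to change.** 1. In section 2.5.4, replace the sentence on changes with a correlation, with 95% CI, of pre-treatment tumour expression with baseline plasma expression, separately for PD-L1 and IFNγ, in patients with usable paired samples. Report the number of pairs.
2. Name Spearman as the default. If Pearson is preferred, state the transformation applied to the RT-qPCR and ddPCR values.
3. If baseline tumour level is also to be correlated with later change in blood, list it as a separate question under its own label.
4. In section 1.2.6, say that tumour is measured at baseline and blood at several time points. If repeat tissue is in fact planned, state its timing in section 2.4.2 instead.
5. Report the interval between tissue and baseline blood. Section 2.4.2 sets no window for tissue beyond its being pre-treatment, while baseline blood falls within 4 weeks before treatment, and section 1.2.4 itself says that PD-L1 varies over time and between primary tumour and metastases.

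The cost is a few sentences and no new samples. What is given up is any suggestion that on-treatment blood changes have been shown to follow changes in the tumour.
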